#### Phase 4 (Objective 4): Describe Parent and Child Outcomes of Naître et Grandir+ Information Use

##### Design

We will conduct a qualitative interpretive study to generate an in-depth description of parent and child outcomes from the parents’ perspective [124]. On the basis of our systematic review [66,67], we anticipate 3 types of parent outcomes (decreased worries, increased confidence, and self-management) and 2 types of child outcomes (prevented problem and improved development, health, and well-being). Our pilot data (34,021 IAM ratings) also suggest parents rarely report potential negative consequences of using information, for example, vaccine adverse effect (n=183; 0.5%). In outcomes research, qualitative methods are appropriate for exploring complex outcomes from the stakeholders’ perspective, such as life experiences [111,125-131]. In our study, information can influence parent decision making, but the relationship between information and decision is not simple. Our qualitative study will (1) identify causal events, (2) map them in a complex causal network, and (3) build a chronological chain of qualitative evidence between N&G information and a parents’ decision that affects knowledge, attitude, or behavior [131,132].

##### Participants

Participants who received the N&G+ newsletter, used IAM+ at least once, have agreed to be contacted for research, and live in a high deprivation area will be approached for recruitment. The recruitment procedure will be the same as for phase 1. In 2015, more than 24,000 families received, upon request, the weekly newsletter. We will begin by recruiting 30 parents (and continue recruitment, as needed, to achieve data saturation) who report, via IAM+, positive health and well-being outcomes and/or potential negative consequences of information (prioritizing those who live in the areas of highest deprivation). As we are looking for individual stories for about 6 types of outcomes (some less frequently reported than others), data saturation may not be reached with fewer than 50 participants [111,133-135].

##### Data Collection

The research assistant having experience in qualitative interviews with low-SES persons will conduct 60-min face-to-face interviews to elicit participants’ IAM+ ratings. The interview guide will be based on our theoretical model (Figure 2) and input from team members and the steering committee. To stimulate recall (memory), the interviewee will be given the list of recent texts they rated and their ratings. For each newsletter, the research assistant will ask open questions regarding what happened to them and/or their children that led them to report an expected outcome (positive or negative). Participants will be interviewed twice 3 months apart to increase the number of described outcomes and avoid fatigue of long interviews. Participants will receive Can $20 per interview as compensation for their time. In addition to the research assistant’s observation notes, interviews will be audio recorded and transcribed verbatim.

##### Data Analysis

Two principal investigators (PP and CL) have experience in qualitative research. With the research assistant, a collaborator anthropologist having expertise in life histories (MB) and a research trainee will read notes and interviews and meet regularly. For each case (information used with at least 1 outcome experienced by a parent and a child), they will interpret the data in the form of a *small story* [112,136-138]. This method allows researchers to describe a person’s individual experience (including all perceived influences) and helps the researcher understand the individual’s attitude and behavior [33]. In research meetings, 2 questions will be answered through recorded discussion of arguments for and against each analytical decision (rigor based on sharing reflexivity): is the case story clear? and are the causal network and chain of evidence trustworthy? Disagreements about clarity and trustworthiness of case stories will be resolved with 3 other team members having experience in qualitative research ([name], [name], and [name]). Case stories will be reviewed by all team members and the steering committee. This may detect issues and result in the principal investigators and research assistant revising parts of their analysis.

##### Anticipated Results

This will generate up to 10 case stories per outcome type, being the first in-depth qualitative description of low-SES parents’ perspective on outcomes of online child information use.

## Results

The project was funded in 2017 by the CIHR and received an ethics approval by the McGill University’s IRB. Data collection for phase 1 was completed in 2018. Phases 2 to 4 will be completed by 2020. Findings from this study will be used to develop a free toolkit, useful to all Web editors, with recommendations for improving health information for low-SES persons and interactions with them using IAM. Results will be published in peer-reviewed journals and presented at national and international scientific conferences.

## Discussion

### Direct Impact on
*Naître et grandir* and
*AboutKidsHealth*

Any improvement of knowledge translation tools and websites such as IAM, N&G, and AKH can have an important impact as it affects a large population of individuals with a low literacy level. In fact, the effectiveness of childhood education interventions has been demonstrated repeatedly [16-19,23,27-47]. In our 2-year pilot data, parents expected health and well-being benefits (for themselves or their child) from using N&G information in 65.4% of all IAM ratings (n=34,021) [50]. In accordance with knowledge translation and implementation research [62], we will not replicate effectiveness studies and rather focus on improving interventions that work.

Our project can improve engagement (number of visits) with websites providing high-quality low literacy information; in turn, online parenting information improves parents’ knowledge, attitudes, and behaviors [139-145]. Given our integrated knowledge translation (participatory research) approach, N&G and AKH will adapt their content for low-SES users as we generate results. In addition, IAM+ will better support low-SES parents’ interactions with Web editors and empowerment. Thus, our results can immediately benefit millions of information users with a low literacy level (children’s parents and relatives), for example, in Canada (Table 3).

IAM+N&G+ can be seen as an innovative intervention that complements traditional literacy programs (eg, family literacy classes). Indeed, interventions that somewhat compensate for a low literacy level can greatly improve parents’ and children’s health and well-being [23]. Thus, our results can have a positive impact on 55% of the Canadian working age, those who have a low level of *health literacy* and need compensatory help to manage their health [23,89,90].

Specifically, IAM+N&G+ can help Canadians in francophone minority communities, as 500,000 annual N&G website visits originate from them. Research with these communities is very underfunded, thus a CIHR priority [146]. As stated in the October 2016 report of the Commissioner of Official Languages [147], early childhood development in these communities *is hindered by a lack of resources*, and *the absence of specific funding* has left them *vulnerable and often incapable of meeting their needs*.

**Table 3 table3:** Targeted population in Canada.

Across Canada	IAM^a^ *Naître et grandir* (new version)	IAM *AboutKidsHealth* (new version)
Families^b^	1.3 million families have French as mother tongue (couples with children and single-parent families with at least 1 child)	5.8 million families (couples with children and single-parent families with at least 1 child)—all languages
Children’s parents and relatives^b^	2.8 million adults aged 20 to 69 years have a low literacy level (and French as mother tongue)	12 million adults aged 20 to 69 years have a low literacy level
Website visits from Canada	8.3 million^c^ visits in 2015 mainly from Quebec (7.8 million), Ontario (304,000), and New Brunswick (70,000)	1.5 million visits in 2015 mainly on Web pages in English (58%), French (16%), Spanish (14%), and Arabic (5%)

^a^IAM: Information Assessment Method.

^b^Statistics Canada 2015.

^c^76% of parents of children aged under 8 years consult *Naître et grandir* in Quebec (on average 1.3 times per week).

### Potential Impact Beyond
*Naître et grandir* and
*AboutKidsHealth*

Results will inform the development of an open access online tool kit on how to adapt websites and IAM+ for a low literacy audience (a growing consideration of many Web editors). The tool kit will be designed to be generalizable to all types of online consumer health information in Canada. It will include guidance with 3 main messages: (1) how to produce simple information in lay language with audio and visual content, (2) how to better interact with low-SES persons using IAM+, and (3) how to use consumers’ IAM+ ratings and feedback to continuously optimize information content. The tool kit will be freely available to any Web editor via the Quebec SPOR-SUPPORT Unit and IAM websites. The NPI has experience in developing tools and leads the method development platform of the Quebec SPOR- SUPPORT Unit.

Our primary knowledge translation goal for knowledge user audiences will be to raise awareness about our main messages and drive attention to the tool kit. A secondary knowledge translation goal will be to support the implementation of the toolkit by Web editors. Knowledge users will disseminate our work in multiple Canadian organizations. As per reviews on scaling up [148-150], we will update our 2016 environmental scan and contact all Canadian websites targeting parents. A specialized librarian (collaborator) will reach additional health websites through librarian listservs and peer networks. Team members will raise general awareness for the tool kit and deliver our main messages to a variety of academic and nonacademic knowledge user audiences via a range of knowledge translation strategies (conference presentations, open access peer-reviewed publications, plain language summaries and grey literature, social media, and networks). Multiple knowledge translation channels will be used including Twitter (@UniteSoutien) and websites such as the Quebec SPOR-SUPPORT Unit and the IAM websites [151,152].

### Contribution to Scientific Knowledge

Our project will advance knowledge on the value of online information for, and interaction with, low-SES persons to strengthen health systems. On the one hand, this project is the first to systematically explore health and well-being outcomes for low-SES parents and children associated with parenting information websites. Most studies focus on discussion forums that can be intimidating to low-SES parents [140,142,143,153,154]. On the other hand, many studies concern relational marketing and website feedback buttons [52,155-158], but we know of none that addresses interactions between low-SES persons and Web editors (such as interaction through IAM+).

### Timeline and Potential Challenges

Overall, 3 years will be needed to complete this project (Figure 3). Our phases are simple and well defined, and our planning is realistic. In phases 1 and 4, we anticipate no recruitment difficulties. Many parents have already agreed to be contacted for research, and N&G will facilitate the recruitment. Phase 2 is feasible, and the deliverables are realistic given that N&G has already implemented IAM, McGill and N&G have a strong OPR partnership, and N&G is committed to implementing IAM+N&G+. In phase 3, the large number of N&G readers guarantee a large sample. To control for potential seasonal variation in the number of sessions pre- and postimplementation, monitoring will be conducted during the same seasons. To control for contextual changes, variables such as type of device, age, gender, and location are covariates. We have opted for a prospective longitudinal study as monitoring is embedded in N&G routines. In addition, although randomization would provide a higher level of evidence, it was considered unethical to randomly assign low-SES parents to N&G+ or N&G information and impractical for such a popular website (contamination bias) [159]. Moreover, 3 typical potential sources of biases in longitudinal designs may not affect our study: the use of proportions will control for historical events, there will be no *respondent fatigue* as our 2-year pilot data showed that the monthly number of IAM raters is stable, and the social desirability bias will affect pre- and postimplementation periods in a similar manner.

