**Figure 1 figure1:**
[figure not shown]
Social gradient in assessing *Naître et grandir* (N&G) information with Information Assessment Method (IAM). A dot represents the total number of IAM ratings completed by all N&G newsletter subscribers living within the postal code areas of a Canadian centile of Material Deprivation. There is a negative linear relationship as areas with higher deprivation have a lower proportion of newsletter ratings/subscribers. The correlation coefficient is −.42 (*P*<.001).

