### Goal and Objectives

This study (research protocol) has been recently funded by CIHR. As per CIHR’s definition of knowledge translation (“making people aware of knowledge and facilitating knowledge use to improve health”) [62], our goal is to improve how low-SES parents engage with and use online information about child development, education, health, and well-being; learn how this format for knowledge sharing translates to improved health and well-being outcomes for low-SES parents and their children; and explore their interaction with Web editors to influence content (responsible for websites’ content). On the basis of the N&G team's (the director and 2 coordinators) questions and using the Knowledge-to-Action framework [63], we determined 4 research objectives:

Objective 1: Identify low-SES parents’ views on barriers and facilitators to accessing, understanding, and using N&G information content and to interacting with N&G editors via the IAM.Objective 2: Adapt N&G content/functions and the IAM tool (user-centered design) to reduce barriers and optimize facilitators identified in phase 1 and implement new versions labeled N&G+ and IAM+.Objective 3: Evaluate whether N&G+ and IAM+ result in a higher proportion of low-SES parents engaging with the N&G site and the content provided and interacting with editors via the IAM.Objective 4: Describe how expected health and well-being benefits of N&G+ information use (reported via IAM+) are experienced by parents with low SES and their children.

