##### Measurement

N&G and McGill already use Google Analytics, an objective and reliable automatic data collection of N&G readers’ demographic characteristics and website use behavior (based on javascript codes in each Web page) [117-120]. IAM raters’ demographic data are collected with a questionnaire (linked to an anonymized identifier). The validated IAM questionnaire [53] collects self-reported information use and subsequent expected health/well-being benefits for parents and their child.

**Table 2 table2:** Types of outcomes monitored weekly.

Type	Outcome	Description and data source
A1	N&G^a^ sessions	Weekly number of unique sessions (Google Analytics)
A2	N&G read	Weekly proportion of sessions with at least 1 page entirely read (Google Analytics)
A3	IAM^b^ ratings	Weekly number of IAM questionnaires submitted
B1	N&G mediated	Weekly proportion of IAM ratings information used for the child of someone else
B2	N&G used	Weekly proportion of IAM ratings information used for oneself and one’s child
C	Expected benefits	Weekly proportion of IAM ratings expected health or well-being benefit for a parent and child, including at least 1 of the following self-perceived benefits (IAM choices of response): improvement of the health or well-being of a child, being less worried, prevention of a problem or the worsening of a problem, handling a problem, and being more confident to decide something with someone else

^a^N&G: *Naître et grandir*.

^b^IAM: Information Assessment Method.

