##### Statistical Analysis

Linear mixed modeling will integrate spatial analytics (geomatics) and account for the clustered nature of the data. The pre/post status, the SES quintile of deprivation, and potentially confounding variables will be included as fixed-effects covariates. The inference model will incorporate random effect terms for individual variables and Web page–specific variables. For each outcome, an interaction term of the SES quintile of deprivation and the pre/post status will be included to assess the pre/post change for each quintile. Estimated regression coefficients and variance parameters will be reported along with appropriate confidence intervals.

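### Proportions cannot control for historical events in sessions (A1) and IAM ratings (A3), which are raw weekly counts read as each quintile's own pre/post change

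*Protocol article*

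**What the plan says.** Under Timeline and Potential Challenges, the protocol lists three biases typical of longitudinal designs that it expects not to affect the study. For history, the reason given is that "the use of proportions will control for historical events".

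Table 2 (Phase 3, Measurement) defines six weekly outcomes. A1 is "Weekly number of unique sessions (Google Analytics" and A3 is "Weekly number of IAM questionnaires submitted". The other four (A2, B1, B2, C) are proportions of sessions or of ratings; A2, for example, is "Weekly proportion of sessions with at least 1 page entirely read (Google Analytics".

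Objective 3 asks whether the new versions "result in a higher proportion of low-SES parents engaging with the N&G site" and its content, and interacting with editors through the IAM.

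The Statistical Analysis section plans linear mixed models in which "an interaction term of the SES quintile of deprivation and the pre/post status will be included to assess the pre/post change for each quintile". All Canadian readers and raters are included, and randomization is rejected, so every reader is exposed after implementation. The anticipated result is a rise in every outcome.

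**The concern.** A before/after comparison without a concurrent control cannot separate the intervention from anything else that changed between the two periods. The protocol sees this and offers proportions as the answer for historical events. That answer cannot work for an outcome with no denominator, and A1 and A3 have none. They are also the only measures of how much the site is used and how often parents interact through the IAM.

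Reading the interaction within each quintile does not help, because an event that lifts all quintiles lifts the most deprived one too. Organic growth, publicity or a search-ranking change would then look like better reach among low-SES parents. Phase 3 is the study's quantitative evaluation of IAM+N&G+, and the social gradient was the reason for doing it.

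**Working it through.** The protocol gives no figure on this point to reproduce. The check has two parts.

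**1. Which outcomes the safeguard can reach**

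- A1 and A3 are counts without a denominator. The safeguard cannot apply.
- A2 has sessions as its denominator; B1, B2 and C have ratings. A pure change in volume cancels, but an event that alters who visits or who rates does not.
- None of the six is the share of sessions or ratings that comes from low-SES parents.
- Of the other controls, the same-season windows (9 months before, 3 months excluded, 9 months after, so each window starts 12 months after the other) remove recurring seasonality. Device, age, gender and location adjust for user mix. Neither measures a lasting change in total traffic.

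**2. Size under no true effect**

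Inputs from the protocol: about 5,000,000 sessions and 15,000 ratings per period (Study Size), and 9 months per period (Setting), taken as 39 weeks.

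Assumptions not in the protocol:
- common growth g of 5%, 10% or 20%;
- most deprived quintile's share s of 20%, 15% or 10%, paired with a least deprived share of 20%, 25% or 30%;
- Poisson weekly counts, for the z values only.

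Formulas:
- pre = total × s / 39; post = pre × (1 + g)
- z = (post − pre) / √[(pre + post) / 39]
- linear interaction = change in most deprived − change in least deprived
- ratio of ratios = (post/pre in most deprived) / (post/pre in least deprived)

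Middle case, g = 10%, shares 15% (most deprived) and 25% (least deprived):

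| | A1, sessions/week | A3, ratings/week |
|---|---|---|
| Most deprived, pre | 5,000,000 × 0.15 / 39 = 19,231 | 15,000 × 0.15 / 39 = 57.7 |
| Most deprived, post | 21,154 | 63.5 |
| Within-quintile change | +1,923 (+10%) | +5.8 (+10%) |
| Poisson z | 59.8 | 3.3 |
| Least deprived, change | +3,205 | +9.6 |
| Linear interaction | −1,282 | −3.8 |
| Ratio of ratios | 1.10 / 1.10 = 1.00 | 1.00 |
| Most deprived share, pre and post | 15%, 15% | 15%, 15% |

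Over the whole assumed range, the spurious within-quintile change is +641 to +5,128 sessions per week (z 24.7 to 134.8) and +1.9 to +15.4 ratings per week (z 1.4 to 7.4). Real weekly counts vary more than Poisson, so these z values are upper guides. They show that large volume makes the spurious signal look firmer and does not remove it.

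The linear interaction is zero only when the quintiles have equal baselines. With the unequal baselines above it runs from −641 to −5,128 sessions per week, a false widening of the gap. The share and the ratio of ratios are unaffected in every case.

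**The case against.** The strongest reply is that the plan already holds what is needed. A quintile-by-period interaction is fitted and coefficients with confidence intervals will be reported, so a uniform lift would show as movement in all five quintiles. This stands in part: the analysis is not missing. But the protocol gives the term a within-quintile reading, and on a linear count scale its coefficients do not cancel a proportional shift unless baselines are equal.

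Second, Objective 3 can be read as the proportion of low-SES parents who engage, not their share of all traffic, and the other quintiles also receive the new version, so they are not true controls. This stands as a limit on the remedy: if N&G+ raised use equally everywhere, a between-quintile contrast would show nothing although more low-SES parents engaged. It does not rescue the claim about proportions, because a raw count is not a proportion on either reading.

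Third, the pilot showed a stable monthly number of IAM raters. That makes drift in A3 less likely, but it says nothing about sessions or about the study period itself.

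Some stronger readings are not supported:

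- A reader might infer that any traffic shift is mistaken for an effect. Recurring seasonal shifts are handled by the matched windows, and the first 3 months after launch are excluded.
- A reader might infer that general growth would be declared a success. The protocol states no decision rule.
- A reader might add a false-positive rate over six outcomes and five quintiles. The protocol states no significance level, and the outcomes are not independent, since B1, B2 and C come from the ratings counted in A3.
- A reader might take the Figure 1 measure, where "areas with higher deprivation have a lower proportion of newsletter ratings/subscribers", as a ready denominator for A3. Figure 1 concerns newsletter subscribers, whereas phase 3 counts all raters.

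**Conclusion.** The statement about proportions is wrong for A1 and A3 and right only in part for A2, B1, B2 and C. A non-seasonal change common to the quintiles passes in full into the most deprived quintile's count: growth of g appears as a change of g, while the quintile's share and the ratio of changes do not move. That conclusion follows from the outcome definitions and the stated contrast. The weekly figures depend on the assumed growth and shares, and whether such a change will occur is unknown. The planned within-quintile changes remain useful description, but they cannot by themselves support a claim that low-SES parents in particular gained.

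**What to change.** 1. In Timeline and Potential Challenges, limit the statement to A2, B1, B2 and C, and say that their denominators cancel pure volume changes only.
2. For Objective 3, add the most deprived quintile's weekly share of Canadian sessions and of IAM ratings. Equivalently, take the difference in log pre/post change between that quintile and the others from a count model with a log link.
3. Base any claim of a specific low-SES gain on that contrast. Report the within-quintile changes in A1 and A3 beside it, labelled as uncontrolled for history.
4. If ratings per subscriber are used as well, restrict the numerator to newsletter ratings.

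Cost: no new data, since sessions and ratings are already assigned a deprivation index. The log-link option is a change of model for the counts, not only of wording. Intervals will be wider than for the within-quintile change. The contrast shows only a differential effect, so it is conservative if N&G+ raises use in every quintile.
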